### Blinding

Treatment allocations will be blinded to the participants, clinicians, research assistants, drug managers, statisticians, and other staff members, and will not be revealed until the study is completed. After a run-in period, the clinicians will assess whether the patients are still eligible. For each eligible patient, the clinician will apply for a randomized assignment by logging into the web-based randomization system, and write a prescription for “TCKM granules, three bags, twice a day.” Then, accompanied with a research assistant, the patients will be taken to the appointed drug managers at the GPHCM pharmacy. The drug managers are responsible for dispensing medication according to the prescriptions and assignments. During the trial periods, clinicians, research assistants, and drug managers are forbidden from discussing the assignment possibilities with the participants. The placebo granules have an appearance, smell and taste similar to the TCKM granules. All drugs are packaged in an identical manner. The blinding codes will be kept strictly confidential, and will not be broken during the trial unless serious adverse events occur. The date and reason for breaking the blinding code will be recorded in the case report forms (CRFs).

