### Safety assessments

All participants must undergo an electrocardiogram examination and a series of clinical laboratory tests before and after the treatment (weeks 0 and 4). These will include routine blood, urine, stool, and stool occult blood, kidney function, and liver function tests. More attention will be given to the abnormal changes found in the examinations and, when necessary, a re-examination and a causality assessment will be required.

No reports of harm to patients exist from long-term clinical observations with TCKM granule treatment. Nevertheless, participants will still be instructed to report any adverse events (AEs) during the trial. The clinicians will be in charge of managing AEs. An independent Data and Safety Monitoring Board (DSMB) from GPHCM will be in charge of studying each case individually to access any serious adverse event (SAE) and the causality between the SAE and the intervention. AE details including clinical manifestations, severity, occurrence time, recovery time, management and causality will be recorded on CRFs. If any SAE occurs, it must be reported to the principal investigator, DSMB, and the Ethics Committee within 24 h, and any necessary treatment will be provided as soon as possible. When necessary, the blinding will be broken and participants will be provided suitable treatments. All SAEs will be followed up until they have been resolved.

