### Sample size calculation

The sample size for this trial was calculated based on the primary outcome—the proportion of responders of AR, using PASS 11.0 software (NCSS, LLC, Kaysville, UT, USA). Combining our previous observational study with similar studies [28, 29], we assume that the proportion of responders of AR in TCKM granule group will be 60%, and in the placebo group 30%. Fifty-seven patients in each group can achieve 90% power and rule out type I error of 5% by using a two-sided test. We expect that 20% of the participants may be lost to follow-up. Therefore, the sample size in each group should be adjusted to 72. In total, 144 participants will be enrolled in this trial.

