### Statistical analysis

Statistical analysis will be performed by blinded specialized statisticians using PASW Statistics 18.0 (IBM SPSS Inc., Armonk, NY, USA) and SAS 9.2 software (SAS Institute Inc., Cary, NC, USA). A level of 5% (two-sided) type I error will be considered as statistically significant. Analysis will be based on both intention-to-treat and per-protocol populations.

Baseline characteristics, which also include predictive factors, will be presented for each group. From baseline to each time point, discrete variables will be described with frequencies and percentages, and continuous variables will be described with either mean and standard deviation for data with normal distribution or median and interquartile range for non-normally distributed data. For comparisons between experiment and control group at each time point, a chi-square test or Fisher’s exact test will be used for discrete variables, and the Student’s *t* test or Wilcoxon-Mann-Whitney *U* test will be used for continuous variables.

The analyses of predictive factors will be performed in two steps as follows: The first step is univariate analysis. The AR post-treatment (week 4) and follow-up (week 16) responder rates will be used as dependent variables, and predict factors, such as demographic and clinical characteristics, and key elements of CM patterns, will be used as independent variables. A logistic regression analysis will be conducted. The selection criteria for the independent variable is defined as α = 0.1. The second step is multivariate analysis. Those predictive factors selected through the first step will be entered into two multiple regression models, taking the post-treatment (week 4) and the follow-up (week 16) AR responder rates as the dependent variable. Each model will be conducted to adjust or unadjust for initial baseline level including scores of IBS-SSS, IBS-QOL, and HADS.

We plan to do some sensitivity analyses. Firstly, we will compare the primary and safety outcomes between all randomized patients and unmasking patients. Secondly, we will test the impact of the missing data on our primary outcome. The method of multiple imputations will be used to handle missing data. We will compare the results of primary outcome using the multiple imputed dataset and un-imputed dataset to test robustness.

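### The first sensitivity analysis sets all randomised patients against the unmasked ones, so it cannot show whether the TCKM effect is robust to unmasking

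*Protocol article*

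**What the plan says.** The Statistical analysis section of the Protocol article announces two sensitivity analyses. In the first, "we will compare the primary and safety outcomes between all randomized patients and unmasking patients". The sentence does not mention treatment arm.

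The second concerns missing data: "We will compare the results of primary outcome using the multiple imputed dataset and un-imputed dataset to test robustness". That is one result computed on two versions of the data.

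The same section defines the main contrast as one between arms ("For comparisons between experiment and control group at each time point") and the populations as follows: "Analysis will be based on both intention-to-treat and per-protocol populations".

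Two places say when a patient can become unmasked. The Blinding section says the codes "will not be broken during the trial unless serious adverse events occur", and that the date and reason for a break go into the case report form (CRF). Safety assessments, in its text on SAEs, adds: "When necessary, the blinding will be broken and participants will be provided suitable treatments". An SAE is thus the stated route to a code break, but not every SAE need lead to one.

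**The concern.** A sensitivity analysis for unmasking should ask whether the difference between TCKM and placebo changes when patients whose code was broken are handled differently. The analysis as written asks whether the unmasked differ from everyone, which is another question. Its answer would reflect who gets unmasked rather than what the treatment does.

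If it were carried out literally, the trial report could present it as evidence of robustness, or of fragility, when it is neither. On SAEs the unmasked would look worse because an SAE is what put them in that set.

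**Working it through.** **The plan's own figure.** The inputs are AR rates of 60% and 30%, two-sided 5% and 90% power (Sample size calculation). With pooled variance under the null:

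n = [1.96·√(2·0.45·0.55) + 1.2816·√(0.6·0.4 + 0.3·0.7)]² / 0.30² = (1.379 + 0.860)² / 0.09 = 55.7, so 56 per group.

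The plan states 57, which gives 90.7% power by the same method. Then 57 / 0.80 = 71.25, so 72 per group and 144 in total. The figures reproduce and are not in dispute.

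**1. The contrast does not contain the treatment effect.** With 1:1 allocation, pooled AR in all randomised patients is (60% + 30%)/2 = 45% under the planned effect. With no effect at 45% in each arm it is (45% + 45%)/2 = 45%. The all-randomised side is the same whether TCKM works as planned or not at all.

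**2. The sets overlap.** Every unmasked patient was randomised and is counted on both sides, so the sets are not independent samples.

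**3. The second set is selected by outcome.** Under the Blinding section an unmasked patient has had an SAE, so the SAE rate in that set is 100% by construction. This strict circularity applies only to SAE counts. For AR, non-serious adverse events, laboratory tests and electrocardiogram, the problem is selection on an event after randomisation.

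**4. Timing is ignored.** AR responder status comes from the 4-week treatment period (Primary outcome), but follow-up runs a further 12 weeks (Design). A patient unmasked in follow-up gave every treatment-period AR answer while blinded, yet still counts as unmasked.

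**5. The set is probably very small.** The documents give no SAE or code-break rate. The table rests on assumed rates, with expected number = 144 × s × f and P(none) = (1 − s·f)^144.

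| SAE rate s | share unmasked f | expected number | P(none) |
|---|---|---|---|
| 1% | half | 0.7 | 49% |
| 1% | all | 1.4 | 24% |
| 2% | half | 1.4 | 24% |
| 2% | all | 2.9 | 5.5% |
| 5% | half | 3.6 | 2.6% |
| 5% | all | 7.2 | 0.1% |

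The approximate 95% half-width for an AR rate near 45% is 1.96·√(0.45·0.55/m): 56 points for m = 3 and 37 points for m = 7.

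**6. Cost in power of a proper version.** Take the between-arm AR test with 72 per group and no dropout: (0.30 − 1.96·√(0.495/72)) / √(0.45/72) = (0.300 − 0.1625)/0.0791 = 1.74, so power is 95.9%. Dropping 1, 3 or 7 unmasked patients, all from one arm, leaves 95.8%, 95.5% or 95.0%, if response rates are unchanged by the exclusion.

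**The case against.** The strongest defence is that the sentence is loosely worded. Its neighbour compares results across two versions of the data, so the first item may mean repeating the TCKM-versus-placebo comparison with and without the unmasked patients. That may well be the intent, but it is not what the text says, and on that reading too the sentence needs correcting.

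A second charitable reading is the between-arm result in everyone beside the same result within the unmasked. That does not work either. With 3 unmasked patients, equally likely to come from either arm, the chance that all are in one arm is 2 × 0.5³ = 25%. Otherwise the split is 2 against 1, and the smallest possible two-sided Fisher p is 1/3.

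Nor can the point be set aside as detail that an article leaves to a fuller document. The analysis is stated, and stated wrongly.

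Other parts of the defence stand:

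- A reader might infer that the whole safety comparison is circular. Only the SAE count is.
- A reader might infer that the trial is left without protection against expectation bias in a patient-reported outcome. The document does not present this analysis as a test of blinding success. Such bias would come from patients guessing their arm, which a few code breaks after SAEs neither cause nor measure. Whether patients are asked to guess their treatment is a separate matter that an article may leave out.
- The size of the unmasked set is assumed, not documented.
- Excluding unmasked patients also conditions on a post-randomisation event, and counting all of them as non-responders would overwrite valid answers given before a break in follow-up. The fix has to allow for both.

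**Conclusion.** The point holds as a fault in one stated sensitivity analysis. As written, it is not a comparison of treatments, it sets a subset against the whole, and the subset is selected by an SAE. It cannot support or refute robustness of the TCKM effect to unmasking. This follows from the Statistical analysis and Blinding sections read together and needs no assumed figure.

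The size is limited. About 0.7 to 7.2 of 144 patients would be expected in the unmasked set, if SAE rates are 1% to 5% and half or all of those patients are unmasked. Possibly there would be none. The stronger inference, that the primary result or the sample size is compromised, is not supported: the between-arm test, the intention-to-treat and per-protocol analyses and the 144 patients are all untouched.

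**What to change.** Replace the sentence with an analysis that keeps the arms in view:

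- Compare TCKM with placebo on AR and safety in all randomised patients, and repeat the comparison with unmasked patients excluded.
- For AR, repeat it once more, counting as non-responders only those whose code was broken before the week 4 AR assessment was complete. This is deliberately conservative for anyone who had already answered yes twice.
- Do not test unmasked against all patients on safety. List the unmasked by arm, with the date and reason that the CRF already records.
- State that the all-randomised result stays primary, because both repeats depend on an event after randomisation.

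The cost is a few lines of text and no new data collection. Trial status gives recruitment as still in preparation, so the wording can be settled before the first patient is randomised. The loss of power from exclusion is under one percentage point across 1 to 7 patients (95.9% to 95.0% at most, under the assumptions above).

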### Protocol amendments

A formal amendment to the protocol will be required, and must be approved by the principal investigator and the Ethics Committee of the GPHCM prior to implementation, if modifications may affect the conduct of the study, patients’ potential benefit or safety.

## Discussion

As far as we know, this will be the first study to characterize the responders of treatment outcome along multiple dimensions for IBS in the CM field. This will also be the first study to focus on evaluating the recurrence of IBS symptoms with a series of special definitions of relapse incidents. Compared to previous studies of CM for IBS, this study will have more rigorous methodology and quality assurance.

Relapse is frequent among IBS patients, often leading to repeated clinical visits and missed work. Previous studies have usually been interested in evaluating the short-term effectiveness of an intervention, while recently more attention has been transferred to long-term effectiveness [30]. We have yet to find special outcome on the assessment of IBS relapse. Most studies have evaluated long-term effectiveness by repeatedly measuring common outcomes at each visit. However, the variation in conditions between two visits often is not readily available. Based on clinical practice, we make a series of special definitions of relapse incidents, including time until relief, time until first relapse, and total relapse times. These may be more appropriate for relapse assessment.

Some studies have suggested that in order to achieve a better understanding of the variation in patients’ responses to treatment effects, study populations should be described along multiple dimensions [31]. Doing this may also help to identify more suitable patient populations and optimize the indication. Current studies that have investigated predictive factors have usually been interested in gathering conventional variables such as demographic, clinical, and psychological characteristics [32]. Meanwhile, several potential important factors, such as biological characteristics and environmental factors, have been ignored [33]. Compared with previous studies, our study collects predictive factors along the multidimensional nature of IBS. In addition, due to the specificity of CM’s theoretical system, factors associated with CM, including the CM pathogenesis and symptom patterns, are also taken into account in this trial.

According to the CM theory, *Gan-qi* stagnation and *Pi-qi* deficiency are the basic pathogenesis for IBS [34, 35]; dietary intolerance and emotional disorders are two main causes, making IBS symptoms occur or recur [15]. TCKM granules are comprised of herbal medicine with the actions of regulating the function of the *Gan* and *Pi*, and resisting impacts of dietary and emotional factors. Therefore, TCKM granules could reduce IBS symptom relapse.

The results of this trial should provide high-quality evidence on the efficacy and safety of TCKM granules for IBS and more accurate indication of TCKM granules. Importantly, this trial will provide a novel research method for clinicians and researchers to improve the effectiveness of CM.

## Trial status

Participant recruitment is in preparation.

## Abbreviations

AE: Adverse event
DSMB: Data and Safety Monitoring Board
AR: Adequate relief
BSFS: Bristol Stool Form Scale
CM: Chinese Medicine
CRFs: Case report forms
GMP: Good Manufacturing Practice
GPHCM: Guangdong Provincial Hospital of Chinese Medicine
HADS: Hospital Anxiety and Depression Scale
IBS: Irritable bowel syndrome
IBS-QOL: IBS-Quality of Life Questionnaire
IBS-SSS: IBS Symptom Severity Score
SAE: Severity adverse event
SAS: Self-rating Anxiety Scale
SDS: Self-rating Depression Scale
TCKM: *Tiao-Chang-Ke-Min*
